## Abstract

**Background:**

Asthma is a prevalent chronic disease that is difficult to manage and associated with marked disparities in outcomes. One promising approach to addressing disparities is shared decision making (SDM), a method by which the patient and provider cooperatively make a decision about asthma care. SDM is associated with improved outcomes for patients; however, time constraints and staff availability are noted implementation barriers. Use of health information technology (IT) solutions may facilitate the utilization of SDM. Coach McLungs^SM^ is a collaborative web-based application that involves pediatric patients, their caregivers, and providers in a personalized experience while gathering patient-reported data. Background logic provides decision support so both audiences can develop a well-informed treatment plan together. The goal of this study is to evaluate the implementation of the Coach McLungs^SM^ intervention into primary care.

**Methods:**

Implementation will be evaluated using a stepped wedge randomized control study design at 21 pediatric and family medicine practices within a large, integrated, nonprofit healthcare system. We will measure changes in emergency department visits, hospitalizations, and oral steroid use, which serve as surrogate measures for patient-centered asthma outcomes. We will use a generalized linear mixed models with logit link to test the hypothesis for the reduction in exacerbation rates specifying the fixed effects of intervention and time and random effects for practice and practice*time. This design achieves 84% power to detect the hypothesized effect size difference of 10% in overall exacerbation between control (40%) and intervention (30%) periods (two-sided, *p* = 0.05). Implementation will be guided using the Expert Recommendations for Implementing Change (ERIC), a compilation of implementation strategies, and evaluated using the CFIR (Consolidated Framework for Implementation Research) and RE-AIM (Reach Effectiveness, Adoption, Implementation, Maintenance).

**Discussion:**

We anticipate that a tailored implementation of Coach McLungs^SM^ across diverse primary care practices will lead to a decrease in emergency department visits, hospitalizations, and oral steroid use for patients in the intervention group as compared to the control condition.

*Trial Registration*: Clincaltrials.gov, NCT05059210. Registered 28 September 2021, https://www.clinicaltrials.gov/ct2/show/NCT05059210

**Supplementary Information:**

The online version contains supplementary material available at 10.1186/s12911-022-02030-1.

## Background

Asthma is a respiratory disease affecting the lungs which results in significant illness and death regardless of age. In the United States, asthma is one of the top chronic diseases affecting over 6 million children, with 80,000 hospitalizations, 185 deaths, over 500,000 Emergency Department (ED) visits, and more than 7.9 million missed school days every year [1–9]. Significant disparities in asthma outcomes occur by sex, race, ethnicity, and socioeconomic status [10–19]. Pediatric males have a higher prevalence of asthma and are more likely to have inpatient stays for asthma [14, 15, 20, 21]. Minority children are less likely to utilize controller medication [10, 11, 22–27] with African American children having 2 to 3 times higher rates of acute care visits compared with non-Hispanic white children and a 4.9-fold higher asthma death rate [10, 11, 28–31]. Inner cities, such as Charlotte, NC, are epicenters for asthma health disparities in the US, with children 10–17 years old bearing a disproportionate share of the burden [32–35].

Numerous individual- (provider, patient), interpersonal- (family), and system-level (healthcare policies, health systems operations) factors contribute to poor asthma outcomes [22, 36–42]. These documented disparities may persist due to the lack of a comprehensive approach for asthma care that is scalable, sustainable, and widely disseminated [22]. Previous programs, such as asthma action plans [43], allergen remediation [36, 37, 44–46], education [24, 47–49], peer support [50], case management [51–53], or community health workers [54–57], have shown positive results on a local level or in the short-term; however, no single program demonstrated widespread and sustainable outcomes improvement.

Improved asthma outcomes are associated with effective communication strategies between patients and providers [58–60]. Shared decision making (SDM) is a patient-centered process based on a platform of motivational interviewing, in which patients and providers work together to make decisions, select tests, treatments, and jointly create care plans based on evidence that balances risks with patient preferences and values. Previous studies show this SDM intervention is associated with improved outcomes for pediatric and adult patients with asthma [6, 61–67].

Clinical uptake of SDM has been slow [6, 68, 69] in part because of knowledge gaps on how to best implement and sustain complex interventions. Barriers, such as time constraints, limited support staff availability to serve as health coaches, lack of clinic resources, pressure on clinical sites to improve efficiency, and the complexity of electronic medical record (EMR) systems were noted implementation challenges in previous work. One example of a sustainability barrier is extra staff required to serve as coaches for a paper-based version of the asthma SDM tool [70–73]. While practice facilitation of complex interventions in primary care can show improved outcomes [74, 75], these approaches continue to show mixed results [76, 77].

Implementation challenges combined with rapidly advancing availability of new technologies, led to the development of a health information technology (IT) solution that removed known barriers to adoption and automated the health coach role, thus removing the need for a clinical staff member to serve as the health coach. Specifically, several key elements of SDM are now integrated into an collaborative on-line application called Coach McLungs^SM^.

This Coach McLungs^SM^ health IT solution virtually incorporates elements of in person SDM discussion using a conversational style through Coach McLungs^SM^ to (1) elicit patient asthma information, (2) provide personalized education, and (3) incorporate motivational interviewing [62]. Designed for the user to complete the experience prior to an asthma-specific clinic visit, the application offers patients and caregivers asthma education and opportunities for a more in-depth visit with their care providers. Use of this technology will extend healthcare professionals’ ability to deliver personalized care using an on-line health coach. In summary, Coach McLungs^SM^ integrates elements of the full facilitated approach into a SDM solution that is compatible with primary care practice workflows.

A paper version of Coach McLungs^SM^ was rigorously evaluated in previous studies [6, 61, 64]. This SDM intervention was associated with improved outcomes for both pediatrics and adults, such as reduced ED visits, hospitalizations, decreased rescue medication use, better adherence to asthma control medications, improved asthma-related quality of life, fewer asthma-related medical visits, better lung function, and improved perceptions of SDM [6, 61, 63, 64, 78]. The newly developed virtual version of Coach McLungs^SM^ SDM intervention is currently being evaluated in two pediatric EDs within separate healthcare systems [79].

Implementation research is required to best translate research findings into clinical care and enhance sustainability and ease of dissemination [80]. Implementation and dissemination was highlighted as a key national priority by the National Institutes of Health (NIH), Patient-Centered Outcomes Research Institute (PCORI), the Agency for Healthcare Research and Quality (AHRQ) and the Institute of Medicine (IOM) [81–83]. Yet, researchers are challenged to find reproducible implementation strategies. Implementation evaluation frameworks can offer consistent language and uncover identification of effective strategies across diverse healthcare settings. In recent years, multiple frameworks have been developed to provide guidance on how to evaluate implementation interventions (e.g. the Consolidated Framework for Implementation Research (CFIR) and Reach, Effectiveness, Adoption, Implementation, Maintenance (RE-AIM)) and even more recently, practical guidance and strategies on how to best organize implementation strategies have become available [80, 84, 85], such as the Expert Recommendations for Implementing Change (ERIC), a compilation of implementation strategies [80, 84, 85], that outline key implementation elements and evaluation strategies for use in primary care.

This study will evaluate the implementation of Coach McLungs^SM^ into primary care practices across a large healthcare system. We anticipate the implementation of Coach McLungs^SM^ into primary care will promote understanding of best practices for SDM adoption, improve outcomes for asthma patients, and through ease of use, will be sustainable and facilitate further dissemination of SDM interventions into other primary care settings both locally and nationally. End-users of this intervention will be patients, parents (or caregivers), providers, and practice staff. We anticipate a demonstration of efficacy will improve patient outcomes, particularly for the most at-risk patients. Ultimately, this knowledge may invite appropriate policy changes, such as providing insurance coverage and/or provider reimbursement for SDM, towards further use of SDM interventions.

## Aims and anticipated outcomes

Specific Aim 1: Primary care implementation and evaluation of *Coach McLungs*^*SM*^

Sub Aim 1.1: Convene the Stakeholder Advisory Committee (SAC).

The SAC will consist of researchers, providers, patients, local and national advocacy groups, and other stakeholders as previously described. The SAC will meet to oversee all aspects of the study from inception to dissemination.

Sub Aim 1.2: Implement *Coach McLungs*^*SM*^ at 21 primary care sites within a large healthcare system.

Before randomization, 21 primary care practices selected from 74 eligible practices for *Coach McLungs*^*SM*^ implementation must meet a minimum required number of asthma patients seen within the previous 18 months. Based on our previous experience implementing interventions in primary care practices and the flexibility of the 9-month window for implementation kick-off, we anticipate successful recruitment of all 21 practices within 9 months. After randomization of the 21 practices to the 5 steps of a stepped-wedge study design, we will contact the practice manager at each site to initiate a time for study kick-off lunch-and-learn training. Pre-implementation CFIR and Organizational Readiness for Implementation Change evaluation surveys will take place at study kick-off (see Additional files 1, 2). Practices will be given an iPad for patients to use *Coach McLungs*^*SM*^ in the waiting room or exam rooms prior to their asthma visits. The initial coach session takes 12–15 min to complete, and *Coach McLungs*^*SM*^ will save a personalized summary in the patient’s EMR. *Coach McLungs*^*SM*^ virtual character is adapted into this interactive, virtual form for children aged 5–17 and their caregivers. Preliminary testing with patients and providers across selected primary care practices ensured *Coach McLungs*^*SM*^ adopted appropriate health literacy, technical literacy, and social context [62].

Sub Aim 1.3: Evaluation of the barriers and facilitators to *Coach McLungs*^*SM*^ adoption at the practice and healthcare system level.

Additional provider CFIR evaluations will take place 6-, 12-, and 18-months post-implementation (see Additional files 3–5). Key informant interviews will be conducted at 6-months post intervention (see Additional files 6, 7).

Sub Aim 1.4: Conduct iterative process improvement through ongoing evaluation.

All outcomes and survey data will be collected and provided quarterly to the SAC in order to evaluate the implementation. Barriers and facilitators that emerge from 6-, 12-, and 18- month CFIR post-implementation surveys (see Additional files 3–5) will be reviewed by the SAC and feedback will be provided to the practices at 6-month follow up meetings.

Specific Aim 2: Conduct ongoing evaluation of patient-centered outcomes.

Based on a review of the implementation evaluation literature [61, 86, 87], the RE-AIM framework (Reach, Effectiveness, Adoption, Implementation, Maintenance) will be used for implementation evaluation. Reach, Maintenance: the number of patients and providers utilizing Coach McLungs^SM^ over time at each practice will be measured. As Coach McLungs^SM^ will be accessed through the EMR, we will be able to measure the number of times the intervention is delivered. Effectiveness: Patient health outcomes data of acute care visits for asthma exacerbations will be analyzed for patients who have a diagnosis of asthma (ICD-10 codes J45.0-J45.998) irrespective of intervention, allowing measurement of any outcome improvements over the life of the study. Data will be assessed at 6, 12 and 18 months for patient outcomes.

Specific Aim 3: Dissemination: Disseminate results and strategies for primary care implementation both locally and nationally. We will disseminate through local stakeholders, practice-based research networks, asthma advocacy national organizations, and academic research meetings for healthcare, primary care and asthma. We expect multiple methods, qualitative and quantitative results manuscripts in subsequent years (Fig. 1).

**Fig. 1 Fig1:**
[figure not shown]
Study overview

## Methods

We propose cross-sectional stepped-wedge cluster randomized design with a phased, randomized rollout. Twenty-one practices will be assigned the intervention randomly over the course of 30 months with the first 6 months used as a baseline period (total rollout time period 36 months) [88]. The research team will be blinded to practices that will receive the intervention until 3 months prior to implementation. Randomization is generated by the study statistician using SAS version 9.4, stratified by practice size (Table 1). Once the intervention has been rolled out at the practice, patients will be exposed to Coach McLungs^SM^ as they are seen by providers for their asthma. This implies that crossover to the intervention is not only at the practice level but also potentially the patient level [89]. The patient level exacerbation rates will be measured at 6-, 12-, and 18-month intervals pre- and post- the interaction with Coach McLungs^SM^.

**Table 1 Tab1:** Stepped-Wedge Design for *Coach McLungs*^*SM*^ Implementation with 6-month time intervals for each

	**Baseline (6 mos)**	*Time 1 (6 mos)*	*Time 2 (6 mos)*	*Time 3 (6 mos)*	*Time 4 (6 mos)*	*Time 5 (6 mos)*
Practices 1–4	**120**	*120*	*120*	*120*	*120*	*120*
Practices 5–8	**120**	**120**	*120*	*120*	*120*	*120*
Practices 9–13	**150**	**150**	**150**	*150*	*150*	*150*
Practices 14–17	**120**	**120**	**120**	**120**	*120*	*120*
Practices 18–21	**120**	**120**	**120**	**120**	**120**	*120*

Bold: control period, Italics: intervention period

The aim of implementation is to disseminate Coach McLungs^SM^ to patients most at need in the primary care setting. Often these patients have problems with managing asthma as a chronic disease and adhering to treatment plans. Primary care providers and staff are aware of the need to better prepare patients for chronic asthma management and fully support the Coach McLungs^SM^ SDM intervention.

Inclusion Criteria for this study are: (1) having attained the age of at least 5 years but less than 18 years at enrollment; (2) having established mild, moderate, or severe persistent asthma with a diagnosis verified by practice providers; (3) English or Spanish speaking. 4,981 patients in 21 practices aged 5–17 were seen in primary care for asthma in last 18 months (Table 2).

**Table 2 Tab2:** Number of Primary Care Patients Age 5–17 Diagnosed with Asthma October 2017 to March 2019

	# Eligible patients at proposed 21 practices	# Patients in healthcare system
Aged 5–17	4981	14,283
Male	2985	8528
Female	1996	5755
African American	1995	4863
Caucasian	2364	7147
Other/Unknown	622	2273
Hispanic/Latino	313	1141
Non-Hispanic Latino	4080	10,784
Unknown Ethnicity	588	2358

Providers and clinic staff will offer Coach McLungs^SM^ to all patients and those deemed in need of extra asthma education. To simplify the selection process, practices may choose to offer Coach McLungs^SM^ to all patients with asthma, regardless of asthma severity. An additional enrollment table will track providers who are using Coach McLungs^SM^ at the participating practices. Patient-centered outcomes will be monitored from available EMR data throughout the course of the study by the research team. End-users will be primary care patients, providers, and staff. The types of patients will be primary care pediatric patients and their caregivers (most likely parents) with asthma, aged 5–17 (Table 2).

A key feature of our implementation approach will be the use of iterative process improvement cycles (Fig. 2) to implement this process which will be monitored by the SAC, to evaluate both the process and outcomes of the intervention.

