### Sample size justification

We used a method to estimate sample size that takes into account the cluster randomization and the stepped-wedge design [88]. Our study design includes 21 clusters (facilities) with 6 time periods (including the baseline), 5 steps, 4 facilities switching from control to intervention at each step (except the third step will have 5), and an average of 30 patients per practice being continuously followed. Thirty patients is conservative as the typical number in a 6-month period is approximately 100. We conducted sample size analyses accounting for intracluster correlation (ρ = 0.20), individual autocorrelation (τ = 0.5), and cluster autocorrelation (π = 0.9) [88]. This design achieves 84% power to detect the hypothesized effect size difference of 10% in overall exacerbation between control (40%) and intervention (30%) periods (two-sided, α = 0.05). An effect size of 0.1 translates to a difference between groups of 10% absolute difference between intervention and control overall exacerbation rates.

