### Analysis of outcomes

We will use a generalized linear mixed models with logit link to test the hypothesis for the reduction in exacerbation rates specifying the fixed effects of intervention and time and random effects for practice and practice*time. These random effects are based on the statistical model that accounts for separate correlations among individuals in the same cluster at the same or different time points, and random variation in the secular trends across clusters [89]. To control for repeated measures within individuals, we will include a separate random effect for each patient. We will test the effect of implementing Coach McLungs^SM^ with the intervention fixed effect (two-sided, *p* = 0.05) as well as mean difference and corresponding 95% confidence interval for the intervention effect. The study design and models proposed account for the establishment of causal treatment effects at the patient level [109].

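### The primary model as stated has no term for practice size, although practices are randomised within practice-size strata; adding it is a small, cheap improvement

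*Protocol article*

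**What the plan says.** On allocation, the Methods section states: "Randomization is generated by the study statistician using SAS version 9.4, stratified by practice size (Table 1". The number of strata and their cut-points are not given.

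On analysis, the section Analysis of outcomes sets out a logit-link generalised linear mixed model "specifying the fixed effects of intervention and time and random effects for practice and practice*time". It then adds: "To control for repeated measures within individuals, we will include a separate random effect for each patient". The Abstract names the same fixed effects and the same practice-level random effects. Practice size appears in neither place.

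On design, the section Sample size justification states: "Our study design includes 21 clusters (facilities) with 6 time periods (including the baseline), 5 steps", with four practices crossing over at each step except the third, where five do. It assumes "an average of 30 patients per practice being continuously followed", an intracluster correlation of 0.20, an individual autocorrelation of 0.5 and a cluster autocorrelation of 0.9. The power statement is: "This design achieves 84% power to detect the hypothesized effect size difference of 10% in overall exacerbation between control (40%) and intervention (30%) periods".

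**The concern.** A factor used to restrict the allocation is normally carried into the primary analysis, so that the standard error describes the design that was run. If practices of different size have different exacerbation rates and the strata balance size across steps, a model without size leaves that balanced variation in the between-practice component. Its standard error is then slightly too large.

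The stratum is known for every practice before randomisation, so nothing has to be collected to include it. What is at stake is a little precision and a clean match between design and analysis. The validity of the test is not in question, since an error in this direction is conservative.

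**Working it through.** **Inputs from the article.** 21 practices crossing over 4/4/5/4/4; 6 periods; 30 patients per practice and period; ρ = 0.20, cluster autocorrelation π = 0.9, individual autocorrelation τ = 0.5; 40% against 30%; two-sided α = 0.05.

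**Assumptions.** Linear-scale approximation to the logit model; σ² = 0.40 × 0.60 = 0.24; size balanced across steps; R², the share of the stable between-practice variance explained by size, is not in the article and is varied.

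**Variance components**
- Stable practice variance: ρπσ² = 0.20 × 0.9 × 0.24 = 0.0432.
- Practice-by-period variance: ρ(1−π)σ² = 0.20 × 0.1 × 0.24 = 0.0048.
- Individual variance: 0.8 × 0.24 = 0.192.

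Let a be the part of a practice-period mean's variance that persists over periods and d the part that does not.
- New patients each period: a = 0.0432; d = 0.0048 + 0.192/30 = 0.0112.
- Same patients followed, τ = 0.5: a = 0.0432 + 0.096/30 = 0.0464; d = 0.0048 + 0.096/30 = 0.0080.

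**Variance of the intervention effect.** For this layout:
- U = 63 (treated practice-periods)
- W = 4² + 8² + 13² + 17² + 21² = 979
- V = 4×25 + 4×16 + 5×9 + 4×4 + 4×1 = 229

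Var = 21·d·(d + 6a) / [(21U − W)·d + (U² + 126U − 6W − 21V)·a] = 21·d·(d + 6a) / (344d + 1224a)

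**The plan's own figure first**
- New patients each period: 0.2352 × 0.2704 / (3.8528 + 52.8768) = 0.001121, SE 0.03348. Power = Φ(0.10/0.03348 − 1.96) = 84.8%, which matches the stated 84%.
- Same patients: 0.168 × 0.2864 / (2.752 + 56.7936) = 0.000808, SE 0.02843, power 94.0%.

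The stated figure is therefore reproduced only when the individual autocorrelation plays no part. That is a separate matter; both readings are carried below.

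**Adding the stratum.** Replace 0.0432 by 0.0432 × (1 − R²) in a.

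| R² (assumed) | SE, new patients | SE fall | Power | SE, same patients | SE fall | Power |
|---|---|---|---|---|---|---|
| 0 | 0.03348 | – | 84.77% | 0.02843 | – | 94.04% |
| 30% | 0.03330 | 0.55% | 85.16% | 0.02833 | 0.35% | 94.18% |
| 50% | 0.03306 | 1.25% | 85.64% | 0.02821 | 0.77% | 94.35% |
| 70% | 0.03258 | 2.70% | 86.64% | 0.02797 | 1.59% | 94.68% |

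The gain is small because the stepped wedge relies mainly on within-practice comparison. In a single-period parallel cluster trial with the same inputs, the variance of a practice mean is 0.048 + 0.0064 = 0.0544. R² = 50% would then cut the variance by 0.0216/0.0544, about 40%. Here it cuts it by about 2.5% (1 − 0.9875²).

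**Is there a bias?** Suppose large practices have a rate 10 points higher (assumption) and size is left out. The estimate shifts by Var × 0.10 × Σzᵢ(Uᵢ − 3)/(d + 6a), where zᵢ marks a large practice and Uᵢ is its number of treated periods.
- Size completely sorted by step: the sum is 4×2 + 4×1 = 12 (the third step contributes nothing). The shift is 0.001121 × 1.2/0.2704 = 0.50 points with new patients, or 0.000808 × 1.2/0.2864 = 0.34 points with the same patients.
- First step all large, last all small, the rest balanced: the sum is 8, and the shift is 0.33 or 0.23 points.
- Balanced strata: the shift is 0.

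**Downside of adjusting.** If size has no prognostic value and is fully confounded with step order, including it moves power from 84.8% to 84.1%, a loss of about 0.7 points.

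**The case against.** The strongest reply is that this is a condensed article, that the analysis plan is not shown, and that covariate lists are commonly left to that plan. The model sentence does not say that other covariates are excluded. This limits the point: it concerns the model as the article states it, and the analysis plan may already contain the term. It does not dispose of it, because the article names the primary model's terms in two places and the stratification factor is in neither.

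A second reply is that nothing in the article shows practice size to be prognostic, and that the gain is slight even if it is. Both statements are correct, and they set the size of the point.

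A reader might infer more: that size imbalance across five small steps is left uncontrolled and biases the result. The documents do not support that. Stratification is itself the balancing device, and the practice random effect with within-practice comparison absorbs most of a fixed practice characteristic. Even complete sorting by step, with an assumed 10-point difference by size, shifts the estimate by at most about 0.5 points against a 10-point target.

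A reader might also fault Table 1 for not listing the strata. Its title presents it as the design layout, and the cut-points are detail that the full protocol may hold.

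**Conclusion.** The point holds as a minor, optional improvement. Allocation is stratified by practice size and the primary model as stated has no size term. Including it would lower the standard error by about 0.4% to 2.7% if size explains 30% to 70% of the stable between-practice variance. For shares up to 50% the gain is below 1 power point (at most 84.8% to 85.6%). These figures rest on the assumed share, on balance of size across steps and on a linear approximation to the logit model. Neither material bias nor an invalid test is claimed, and the trial's conclusions would be unlikely to change.

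**What to change.** Add the practice-size randomisation stratum as a fixed effect in the primary mixed model, in exactly the categories used for randomisation, and leave the other terms as they are. If the analysis plan already includes it, align the article's model statement with it; if it is deliberately omitted, one sentence of justification would close the point.

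The cost is one model term. It uses a few degrees of freedom among 21 practices; the exact number depends on the number of strata, which the article does not give. No extra data or change to the conduct of the trial is needed.
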